**Methods:**

We conducted a 2-arm randomized controlled trial for 12 months among employees of an academic health care facility in the United States. The intervention arm received a scale, a smartphone app, an activity tracker, a video library for healthy behavior recommendations, and an on-demand health coach. The control arm received standard employer-provided health and wellness benefits. The primary outcomes of the study included changes in self-reported lifestyle behaviors, cardiometabolic biomarkers, and chronic disease–related medical expenditure. We collected health behavior data via baseline and quarterly web-based surveys, biometric measures via clinic visits at baseline and 12 months, and identified relevant costs through claims datasets.

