## Methods

### Study Design

The UMass Fitbit Care Study is a dual-arm, unblinded randomized clinical trial with a 12-month study period. SPIRIT (Standard Protocol Items: Recommendations for Interventional Trials) reporting guidelines were used in the development of this protocol and fulfilled the SPIRIT checklist [33]. Recruitment began in December of 2020. Participants were randomized to the intervention or control arm using a permuted block randomization that stratified based on age (40 vs ≥40) and sex to achieve a balance for those 2 demographic variables between the intervention and control groups (Figure 1). Participants were randomized 1:1 to a control arm, where participants only received their standard health and wellness benefits during the study period, or an intervention arm, where participants received their standard health and wellness benefits as provided by their employer, plus a digital behavioral change intervention through Fitbit at no cost for 1 year. The Fitbit DBCI included 5 components: a wearable health and fitness device (participant choice of Fitbit Inspire 2 tracker or Versa 3 smartwatch), a wireless weight scale (Fitbit Aria Air), the Fitbit app (provided basic tracking and goal setting functionalities), Fitbit Premium (provided additional advanced metrics and rich video content through the Fitbit app), and an on-demand human health coach (provided goal setting, action planning, and accountability support through secure, asynchronous, in-app messaging).

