### Data Collection and Management

There were four forms of data collected: (1) survey data through baseline surveys and scheduled quarterly surveys for all participants; (2) Fitbit-tracked data for those participants assigned to the intervention arm; (3) biometric data for all participants, which include anthropometric and vital sign measurements and laboratory investigations performed by Quest Diagnostics; and (4) total medical expenditure claims data abstracted by Conifer Health Solutions for all participants. Table 1 describes all the data collected as part of this study. An initial invitation to participate in the study was sent via email to a list of predetermined eligible employees. Interested participants signed up for the study by entering their email address, signing the consent form, and filling out their baseline survey and demographics and presented at an in-person biometric screening appointment performed by Quest Diagnostics staff. At this first visit for the biometric screening, participants in both the control group and intervention group were randomized and scheduled for the 4 follow-up quarterly surveys to study trends in perceptions, motivation, and confidence around improvements in health behaviors. An email was sent to participants each quarter with a link to the quarterly survey in UMass REDCap. Up to 2 reminder emails were sent to participants who did complete the survey. An additional email to all participants was sent in September 2021 to re-engage participants at the three-quarters point of the study. All survey data collection was performed using the REDCap data collection platform. SAS (SAS Institute) was used for all analyses. The final trial dataset, which consists of survey questionnaire data, Fitbit device data, Quest biometric data, and Conifer claims data, is only available to partners within the UMass Chan Department of Population and Quantitative Health Sciences who were responsible for the analysis.

**Table 1 table1:** Data collection schedule.

Events and procedures	Study period (January-December 2021)									Poststudy period
	Enrollment	Allocation	Postallocation				Close-out			
	Visit 0	Visit 1	3 months	6 months	9 months	12 months or visit 2				
Enrollment										
Informed consent	✓									
Demographics	✓									
Eligibility confirmation	✓									
Allocation		✓								
Assessment										
Biometric screening (height, weight, waist circumference, blood pressure, etc)—Quest Diagnostics		✓				✓				

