Baseline survey (nutrition, exercise, sleep, and mindfulness habits)—REDCap^a^	✓									
Quarterly survey (nutrition, exercise, sleep, and mindfulness habits)—REDCap			✓	✓	✓	✓				
Two years of total medical expenditure claims data—Conifer Health Solutions								✓		
Intervention										
Onboarding survey for coaching component		✓								
Engagement data for each component of intervention		Continuous collection of device wear duration Event-based collection of app-open events, feature usage (including Fitbit Premium features), secure messages with coach, etc	Continuous collection of device wear duration Event-based collection of app-open events, feature usage (including Fitbit Premium features), secure messages with coach, etc	Continuous collection of device wear duration Event-based collection of app-open events, feature usage (including Fitbit Premium features), secure messages with coach, etc	Continuous collection of device wear duration Event-based collection of app-open events, feature usage (including Fitbit Premium features), secure messages with coach, etc	Continuous collection of device wear duration Event-based collection of app-open events, feature usage (including Fitbit Premium features), secure messages with coach, etc				
Wearable device and weight scale data		Continuous collection of wearable device data (steps, resting heart rate, sleep metrics, etc) Event-based collection of weight data	Continuous collection of wearable device data (steps, resting heart rate, sleep metrics, etc) Event-based collection of weight data	Continuous collection of wearable device data (steps, resting heart rate, sleep metrics, etc) Event-based collection of weight data	Continuous collection of wearable device data (steps, resting heart rate, sleep metrics, etc) Event-based collection of weight data	Continuous collection of wearable device data (steps, resting heart rate, sleep metrics, etc) Event-based collection of weight data				

^a^REDCap: Research Electronic Data Capture.

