### Statistical Analysis

In this paper, we present descriptive statistics for baseline characteristics and overall engagement among the participants assigned to the intervention group using proportions and the mean for the distribution of categorical and continuous variables, respectively. The study will evaluate its primary objectives using intention-to-treat analysis. A 2-tailed Student *t* test for independent samples will be used to compare the mean of continuous variables, and a chi-square or Fisher exact test will be used to compare categorical variables between the intervention and control groups. Secondary objectives will be evaluated using group-based trajectory modeling to identify distinct trajectories of engagement and adherence, the association of distinct trajectories with baseline behavior and comorbidities, and performing an intervention-only analysis where the treatment effect of the intervention is evaluated across different trajectories of engagement. Additional exploratory analyses will consider accounting for possible contamination based on the self-reported use of wearable health and fitness devices among the control group participants. There are no plans to use biological specimens in ancillary studies. Data collection questionnaires can be provided upon request.

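### Medical expenditure, a primary outcome, is to be compared with an unadjusted t test, although two years of claims probably allow a more precise comparison adjusted for prior-year cost

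*Protocol article*

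**What the plan says.** The Abstract (Methods) states: "The primary outcomes of the study included changes in self-reported lifestyle behaviors, cardiometabolic biomarkers, and chronic disease–related medical expenditure". Read literally, the word changes governs all three groups, expenditure included. Textbox 1 in the Introduction attaches change only to the behaviours and lists expenditure without it.

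The Statistical Analysis section plans an intention-to-treat analysis of the primary objectives. Its one method for continuous outcomes is a two-tailed independent-samples Student t test that "will be used to compare the mean of continuous variables, and a chi-square or Fisher exact test will be used to compare categorical variables". It names no baseline covariate and no separate method for cost, and does not say whether cost is taken as a change or as a study-year amount.

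Study Design describes a "dual-arm, unblinded randomized clinical trial with a 12-month study period", with randomisation stratified by age group and sex. Table 1 lists "Two years of total medical expenditure claims data" without saying which two years. The text above Table 1 describes the same source as "total medical expenditure claims data abstracted by Conifer Health Solutions for all participants", while the outcome is named "chronic disease–related medical expenditure". The Abstract adds that the study "identified relevant costs through claims datasets".

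**The concern.** A person's cost in one year usually carries information about the next. If a pre-randomisation year of claims is in hand, the two analyses that the article's wording allows both make poor use of it. A t test on the change subtracts the whole prior year, noise included. A t test on study-year cost ignores the prior year. Regression on prior cost gives it the weight that the data support.

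This matters more for cost than for the other outcomes. The Introduction expects expenditure to be the most distal outcome with a minimal effect, and the sample size was set by resources rather than by a power calculation. Precision that can be recovered by analysis alone should not be given away.

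A smaller issue is that the outcome and the data carry different labels, so it is unclear which cost enters the comparison.

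**Working it through.** The article gives no cost SD, year-to-year correlation, effect size or power, so there is no stated figure to reproduce.

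**Inputs from the article.** 300 intervention and 303 control participants (Results, Baseline Characteristics); a two-tailed test (Statistical Analysis).

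**Assumptions.** Alpha 0.05; claims available for everyone randomised; one of the two claims years precedes randomisation; equal SD in both years; correlation r from 0.2 to 0.8.

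**1. Relative variance of the arm difference.** Study-year cost alone = 1. Change score = 2(1−r). Adjusted for prior cost = 1−r². The ratio of change to adjusted is 2(1−r)/(1−r²) = 2/(1+r). The last two columns give power at the effect for which the adjusted analysis has 80%.

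| r | Change | Adjusted | Change / adjusted | Study-year / adjusted | Power, change | Power, study-year |
|---|---|---|---|---|---|---|
| 0.2 | 1.60 | 0.96 | 1.67 | 1.04 | 58% | 78% |
| 0.4 | 1.20 | 0.84 | 1.43 | 1.19 | 65% | 73% |
| 0.5 | 1.00 | 0.75 | 1.33 | 1.33 | 68% | 68% |
| 0.6 | 0.80 | 0.64 | 1.25 | 1.56 | 71% | 61% |
| 0.8 | 0.40 | 0.36 | 1.11 | 2.78 | 76% | 39% |

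Adjustment wins at every r between 0 and 1. Below 0.5 the change score is also worse than ignoring the prior year; above 0.5 it is better. In terms of people, a change score on 603 participants is worth an adjusted analysis of 603/1.67, about 362, at r = 0.2, and of 603/1.25, about 482, at r = 0.6.

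**2. Detectable difference at 80% power.** For study-year cost alone it is 2.80 × √(1/300 + 1/303) × CV = 0.228 × CV. At an assumed CV of 2 to 3 that is 46% to 68% of mean cost. At r = 0.2 a change score multiplies this by √1.6 (58% to 87%) and adjustment by √0.96 (45% to 67%). At r = 0.6 the multipliers are √0.8 (41% to 61%) and √0.64 (37% to 55%).

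**3. Effect of skew.** Costs were simulated as lognormal with 10% zeros, 300 against 303, with a CV of 1.5 or 3 for the non-zero costs. With no true effect, the t tests rejected in 4.2% to 4.9% of trials at a nominal 5%. Power for a 20% cost reduction:

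| CV | Raw correlation | Study-year t test | Change t test | Linear adjustment |
|---|---|---|---|---|
| 1.5 | about 0.24 | 42% | 27% | 44% |
| 1.5 | about 0.50 | 40% | 36% | 50% |
| 3 | about 0.18 | 17% | 12% | 17% |
| 3 | about 0.44 | 17% | 14% | 19% |

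Skew leaves the test valid at this size and lowers its power. Linear adjustment is at least as good in every setting, but the margin over a study-year t test is small when the correlation is low.

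**The case against.** The strongest reply is that most of the loss comes from the change score, and only one sentence in the Abstract points to that. Textbox 1 and the Statistical Analysis section do not. If study-year cost is tested, the loss is 4% in variance at r = 0.2 and 19% at r = 0.4. This stands, and it limits the size of the point. It does not remove it, because an unadjusted test is less precise under either reading.

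A reader might go further in several directions that the article does not support:

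- **That prior claims are thrown away.** A change score uses them, only inefficiently. They go unused only if study-year cost alone is tested. That a pre-randomisation year exists is itself inferred from two years of claims for a 12-month study.
- **That skew invalidates the t test.** It does not at about 300 per arm, and the article documents no skew.
- **That power is roughly halved.** For a 30% reduction (log-SD 1.5, 10% zeros, raw correlation about 0.26) a change-score t test had 22% power and a log-link model 45%. That gap needs the change-score reading, a model that ran at 6% to 7% type I error, and an effect well above the minimal one expected. After correction for test size, the log-link model had 44% and the study-year t test 42%.
- **That only a log-link model will do.** Linear adjustment reached 45% to 47% under the same inputs, so the choice of link is a preference.
- **That the wrong cost will be analysed.** The Abstract says relevant costs were identified from the claims, so total claims may simply be the source. The extraction rule may sit in the full protocol or analysis plan, and its absence from an article is not a fault.

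**Conclusion.** The point holds as one of precision. The article fixes an unadjusted t test for a primary cost outcome when the claims probably support adjustment for prior cost. If cost is analysed as a change, the variance is 1.67 to 1.25 times that of the adjusted analysis for r of 0.2 to 0.6. If only study-year cost is tested, the ratio is 1.04 to 1.56 over the same range. These figures rest on assumed correlations, equal SDs in the two years and an inferred prior year of claims. The planned test is not invalid.

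The gain is moderate and does not rescue the outcome. For a 10% reduction, under the skewed-cost assumptions and after correction for test size, every method had only about 7% to 10% power. The difference between total and chronic disease-related expenditure is a labelling matter to clarify, not evidence of a wrong analysis.

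**What to change.** Replace the unadjusted t test for cost with a comparison of study-year cost by arm, adjusted for prior-year cost and the randomisation strata (age group, sex). Linear ANCOVA with robust or bootstrap inference is enough. A log-link model is an alternative if its inference comes from resampling, since robust standard errors alone ran slightly liberal. Report the adjusted mean difference in dollars with its interval. Do not use the change score as the primary cost analysis.

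State which two years the claims cover. If neither precedes randomisation, adjust study-year cost for the strata only.

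Use one label throughout: either say that chronic disease-related cost is extracted from the total claims, or rename the objective as total cost. Because the trial is unblinded, settle this before costs are compared by arm.

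If the prior year is among the claims, no new data are needed. The cost is revised wording and a little more programming.

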#### On-Demand Human Health Coach

Each intervention participant was paired with a personal, human health coach that provided goal setting, action planning, and accountability support for health behavior improvement across activity, nutrition, sleep, and mindfulness, with emphasis on the domains desired by the participant at any moment in time. The health coaches sent a secure, asynchronous, in-app SMS text message within a day of enrollment to each participant to start the process of creating a goal and an action plan for improving the behaviors when the participant’s motivation and confidence were greatest. For example, there might be an exchange of a few messages to determine that a particular user wanted to focus on improving sleep. The coach might help that user set a goal about a regular sleep schedule and an action plan for doing a mindfulness session before bed and not bringing electronic devices to bed (Figure 3).

The health coach then sent a message every day or every other day for the first few weeks to encourage the participant to stick with the plan and to provide support for follow-through or adjustment of the plan. The health coaches monitored core Fitbit data from the users (steps, AZMs, sleep, etc) via a dashboard to help tailor their support. The frequency of messages decreased as the participant gained self-efficacy; however, the option to increase messaging remained if the participant wanted extra support. Each participant was free to use any of the software features of the Fitbit app and Fitbit Premium as desired throughout the course of the intervention, although the health coach made recommendations on features such as workout videos, mindfulness sessions, etc that might be most helpful based on the participant’s goals, action plan, and device data. If participants were unresponsive for several weeks or requested to discontinue coaching, the health coaches archived their profiles in their dashboard and ceased sending them messages unless the participant proactively re-engaged by sending the coach a message.

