## Results

### Baseline Characteristics

A total of 13,391 employees were eligible to enroll in the UMass Fitbit Care Study and received an email or home mailer about participating in the study. Of those invited, 758 completed consent to participate in less than 24 hours and scheduled an appointment for initial biometric screening. The follow-up rate was 75.7%, with 603 individuals attending the biometric screening and getting randomized to the intervention (n=300, 49.8%) or control group (n=303, 50.2%). Baseline characteristics of these 2 groups are provided in Table 2, and no systematic differences were observed between the 2 groups. On average, participants were 46.7 (SD 11.2) years of age. The majority of the participants were female (80.3%, n=484), White (85.4%, n=504), and non-Hispanic (90.7%, n=547). More than half (74.8%, n=440) of the participants had a baseline BMI that classified them as overweight or obese.

**Table 2 table2:** Baseline participant characteristics.

Characteristics		Intervention (n=300)	Control (n=303)	*P* value	
**Age (years), mean (SD)**		46.3 (11.0)	47.2 (11.4)	.34	
**Sex, n (%)**					.50
	Female	241 (80.3)	243 (80.2)		
**Race (intervention: n=295; control: n=295), n (%)**					.80
	White	254 (86.1)	250 (84.8)		
	Black or African American	11 (3.7)	9 (3.1)		
	Asian	20 (6.8)	22 (7.5)		
	Other	10 (3.4)	14 (4.8)		
**Ethnicity, n (%)**					.34
	Hispanic	16 (5.3)	25 (8.3)		
	Non-Hispanic	277 (92.3)	270 (89.1)		
	No answer	7 (2.3)	8 (2.6)		
**BMI classification (intervention: n=297; control: n=291), n (%)**					.56
	Underweight	3 (1.0)	2 (0.7)		
	Normal	65 (21.9)	78 (26.8)		
	Overweight	100 (33.7)	91 (31.3)		
	Obese	129 (43.4)	120 (41.2)		

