### Intervention Engagement and Participant Retention

To approximate real-world scenarios, this study did not have a specific plan to promote participant engagement with the intervention or retention of participants in the study beyond ensuring that their Fitbit device was synced with the mobile app and initial communication with their personal health coach occurred. The median wear time for Fitbit was observed to be 325 (IQR 154-372) days, and 264 (88%) participants used health coaching at least once. Of the 603 participants who completed entrance screening and thus were included in the study, 8 (1.3%) withdrew, 519 (86.1%; intervention: n=251; control: n=268) completed exit surveys, and 469 (77.8%; intervention: n=227; control: n=243) completed exit biometric screening (Figure 4).

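### The engagement objective claims a treatment effect from the intervention arm alone, which has no comparator and can show an engagement gradient even if the programme does nothing

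*Protocol article*

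**What the plan says.** Textbox 2 of the protocol article (Introduction) lists three secondary objectives: engagement trajectories over 12 months, how engagement varies with baseline behaviour and comorbidities, and whether efficacy differs by engagement. The Statistical Analysis section assigns group-based trajectory modelling to them. For the third objective it specifies "performing an intervention-only analysis where the treatment effect of the intervention is evaluated across different trajectories of engagement". Intention-to-treat is stated for the primary objectives only.

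Under Data Collection and Management, the device data are "Fitbit-tracked data for those participants assigned to the intervention arm", so controls cannot be placed in an engagement trajectory. Outcomes are collected in both arms: the article lists "biometric data for all participants, which include anthropometric and vital sign measurements", and surveys and claims also cover everyone.

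The section on the health coach says how exposure changed over time. "The frequency of messages decreased as the participant gained self-efficacy", and "If participants were unresponsive for several weeks or requested to discontinue coaching, the health coaches archived their profiles", after which messages stopped unless the participant wrote again.

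**The concern.** A treatment effect is a difference between what happens with the intervention and what would have happened without it. Randomisation supplies the second part through the control arm. This analysis sets that arm aside and compares more engaged with less engaged people inside one arm. Engagement was self-selected. The article itself sets out to study how it depends on baseline behaviour and comorbidities, and these may also drive the outcome. The coaching rules add a second problem: message frequency fell as people gained self-efficacy and stopped when they went silent, so engagement can be a result of progress as well as a cause of it.

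At stake is the reading of one listed objective. A gradient produced by motivation would be reported as greater efficacy with greater engagement, and a reader could take it as evidence that more use or more coaching produces more benefit.

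**Working it through.** The article gives no sample size, power or alpha for this analysis, so there is no figure of its own to reproduce. The check asks what the planned contrast would show if the programme had no effect at all.

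**Inputs from the article.** Of 300 people randomised to the intervention, 227 had exit biometrics and 251 had exit surveys (Intervention Engagement and Participant Retention). The arm counts printed for exit biometrics, 227 and 243, sum to 470 against a printed total of 469. A difference of one does not matter here.

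**Assumptions, not in the article.** The true effect is zero. The outcome is a change score with SD 1. A latent engagement score has correlation r with the change that would occur anyway. The arm falls into three equal engagement groups. The test is two-sided at 0.05.

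**Step 1: size of the spurious gradient.** The mean of the upper third of a standard normal variable is 1.091, and that of the lower third is −1.091. The expected top-minus-bottom difference is therefore r × 2 × 1.091 = 2.182r SD.

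**Step 2: chance of significance.** With 227/3 = 75.7 per third, the standard error is √(2/75.7) = 0.163 SD. The probability is about Φ(2.182r/0.163 − 1.96). For r = 0.2 this is Φ(0.436/0.163 − 1.96), or about 77%.

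**Step 3: check by simulation** (4,000 runs per row, n = 227).

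| r | Difference (SD) | Top vs bottom, formula | Top vs bottom, simulated | F test over three groups, simulated |
|---|---|---|---|---|
| 0 | 0 | 5% | 4.9% | 4.8% |
| 0.1 | 0.22 | 26.8% | 28.1% | 21.7% |
| 0.2 | 0.44 | 76.6% | 77.3% | 68.2% |
| 0.3 | 0.65 | 98.1% | 98.2% | 96.0% |

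With the 251 exit-survey completers, the F test gives 22.1%, 72.0% and 98.0% at r = 0.1, 0.2 and 0.3.

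**Step 4: the other possible reading.** The phrase could instead mean change from baseline within each trajectory. With 75 people per group and a shift of m SD from secular trend or regression to the mean, the chance of a significant change is Φ(m√75 − 1.96) + Φ(−m√75 − 1.96). This gives 13.9%, 41.0% and 73.8% for m = 0.1, 0.2 and 0.3. That reading does not isolate a programme effect either.

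**The case against.** The strongest reply is that this is the last of three secondary objectives, introduced as characterisation, and that the Conclusions use the language of association for neighbouring work on coaching intensity. On that view the flaw is one of labelling. This is largely right about scope and remedy. It does not remove the flaw, because the article itself fixes the analysis set, the grouping and the quantity to be estimated, and these do not fit together. That is not detail left to an analysis plan.

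The sizes can also be challenged. No passage gives the correlation, trajectory modelling need not yield three equal classes, and the top-versus-bottom contrast is the most extreme one. All of this stands. The figures illustrate what could happen and do not measure a known bias.

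A reader might infer more, in four ways the documents do not support:

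- **A gradient is certain.** It is not. With engagement unrelated to prognosis, the error rate stays near 5%.
- **The contamination analysis shares the flaw.** The article says only that exploratory work will consider "accounting for possible contamination based on the self-reported use of wearable health and fitness devices among the control group participants". No method is fixed, so none can be faulted.
- **Engagement runs past the outcome window.** "The median wear time for Fitbit was observed to be 325 (IQR 154-372) days" is a descriptive result and is not named as the trajectory input. Textbox 2 limits the trajectories to 12 months. Recruitment began in December 2020 and exit screening ended in January 2022, so wear beyond day 365 can still precede an exit visit.
- **The result will set implementation practice.** The statement in Future Aims about informing practice at scale follows a description of further secondary analyses and does not name this one.

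**Conclusion.** The point holds for this secondary objective. The stated analysis has no comparator and conditions on behaviour after randomisation, so it cannot estimate a treatment effect or show that efficacy differs by engagement. It can produce a gradient under a programme that does nothing: 0.22 to 0.65 SD between outer thirds, significant in about 27% to 98% of trials. These figures rest on an assumed correlation of 0.1 to 0.3, equal thirds of 227 completers and an assumed two-sided 0.05. The article makes such a correlation plausible but does not quantify it. The structural conclusion needs none of these numbers. The primary between-arm comparison by intention-to-treat is untouched.

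**What to change.** At the least, reword the third objective in Textbox 2 and the matching sentence under Statistical Analysis. Call the within-arm contrast an association between engagement and outcome change, adjust it for the baseline outcome and baseline covariates, and remove the terms treatment effect and differential efficacy from it. This costs wording only.

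If differential efficacy is to stay an objective, use the control arm:

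1. Model trajectory class on baseline variables in the intervention arm. Relating trajectories to baseline behaviour and comorbidities is already planned.
2. Predict class probabilities for controls.
3. Estimate the between-arm difference within predicted class by principal-score weighting, with a bootstrap interval.
4. State the ignorability assumption and add a sensitivity analysis for unmeasured motivation.

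A complier effect with randomisation as the single instrument would not serve, because it gives one effect and the objective asks about several classes. The costs are wider intervals, an assumption that cannot be tested and some programming. No new data are needed.
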